### Data collection

All data will be collected electronically in an electronic CRF (E-CRF). The E-CRF is a secured website where the participating hospitals must login using a unique password. Participating hospitals will only have access to their own data.

Demographic variables will be collected from all patients, including age, gender, PRE-DELIRIC score, APACHE-II score, and diagnosis group. Furthermore, outcome related variables will be collected (Table 2) as well as variables that may influence the delirium outcome, i.e., dexmedetomidine [32] and early mobilization [33]. Concerning the study medication, we will collect data on the amount of study drug administered as well as open-label haloperidol and other anti-delirium drugs administered in case delirium occurs.

**Table 2 T2:** Primary, secondary endpoints and posthoc analyses

**Primary endpoint**	**Secondary endpoints**	**Post-hoc analyses**
28-day mortality	90-day mortality Delirium incidence	Effectiveness in groups of predicted risk up to 50%, 50–70%, 70–90%, above 90% will be evaluated
	Number of delirium and coma free-days in 28 days	Effectiveness in diagnosis groups: medical, surgical and trauma patients
	Duration of mechanical ventilation	Effectiveness per APACHE-II score: <20, 20–25, >25
	Incidence of unintended tube or catheter removal	Effectiveness in groups with 1, 2, or more positive CAM-ICU scores
	Incidence of ICU re-admission	
	Quality of life measured at time of ICU admission, after 1 and 6 months using SF-12	
	Incidence and severity of side effects of prophylactic haloperidol (all patients)	

### Safety monitoring and safety issues

A Data Safety Monitor Board (DSMB) is established for this study to perform ongoing safety surveillance and to perform interim analyses on the safety data. This is an independent committee composed of two physicians/researchers (a psychiatrist and an anesthetist) and a statistician. The DSMB will perform all interim analyses. To assess side effects of haloperidol and to determine superiority of the intervention or placebo the DSMB will be unblinded for this study, while all researchers remain blinded. Furthermore, the study will be monitored by an independent researcher who will monitor the trial master file, and perform random checks of informed consent forms, drug accountability lists, and source data of primary and secondary outcome measures.

Concerning safety issues, during a patient’s treatment with the study medication, known side effects of haloperidol [34] are pro-actively collected with a special focus on prolonged QTc-time, drowsiness, extrapyramidal symptoms, and agitation and sedation effects. All side effects will be collected during patients’ treatment with the study medication until 24 h after stopping the study medication. In case of the occurrence of side effects, physicians can reduce the dosage or stop the study medication, depending on the severity of the occurred side effect and at the discretion of the attending physician. Only for prolonged QTc-time, strict stopping rules are applied, as described below. To detect side effects of haloperidol, the protocol dictates that patients are physically examined every day for known signs of extrapyramidal symptoms (signs of Parkinsonism and/or akathisia and/or dystonia). Furthermore, daily QTc-time is calculated using a 12-lead ECG or a monitor lead ECG. A QTc-time of over 500 msec combined with an increase of over 10% of baseline QTc-time is defined as prolonged QTc-time. In case of QTc-time prolongation, the study drug is temporarily stopped until QTc-time is normalized. After normalization of QTc-time (<500 msec) the study drug will be restarted. If QTc-time becomes prolonged again, the study drug will be stopped definitively. The patient will remain allocated to the original study group.

To determine long-term side effects, such as rigidity, and quality of life, a recommended and validated quality of life questionnaire, SF-12 [35], is taken at the time of admission and is sent to the patients 1 and 6 months after ICU admission.

The following adverse events will be collected: serious adverse events; non-serious adverse events that are considered by the investigator to be possibly related to the study drug (e.g., prolonged QTc-time, drowsiness, extrapyramidal symptoms, agitation and sedation effects); adverse events that lead to permanent discontinuation of the study drug administration. A serious adverse event is any untoward medical occurrence or effect at any dose that results in one of the following outcomes and is not classified as a clinical outcome of delirium or the underlying disease using the description: death that is not related to the underlying disease or sequel of the underlying disease, or death that is considered by the investigator to be related to the study drug; prolonged inpatient hospitalization or re-hospitalization; a life-threatening experience (that is, immediate risk of dying); persistent or significant disability/incapacity; considered significant by the investigator for any other reason.

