### End of study medication

Prophylactic treatment with haloperidol will be continued until day 28, or discharge from the ICU (whatever comes first), or until delirium occurs. In the latter case, patients will be subsequently treated according to the delirium treatment protocol (with higher dosage of open label haloperidol).

In case delirium occurs, the patient’s study medication (prophylaxis treatment) will be stopped and the patient will be treated with open label haloperidol according to the delirium treatment protocol described below. Analysis will be on intention-to-treat basis. Study medication will not be restarted once delirium subsides, therapeutic haloperidol is stopped, or when a patient is re-admitted to the ICU within 28 days.

#### **
*Delirium treatment*
**

Patients with delirium (defined as a positive CAM-ICU test) will be treated with 2 mg haloperidol intravenously three times daily. Patients suffering from *hypoactive* delirium (only RASS scores between 0 and -3) and patients aged ≥80 years, weighing ≤50 kg, or with liver failure, will be treated with a lower dosage of 3x1 mg intravenously. Dosage can be increased up to a maximum of 3x5 mg in case of serious agitation or anxiety due to delirium. Additionally, midazolam, clonidine, propofol, or dexmedetomidine can be used as an escape therapy in case of serious agitation with insufficient efficacy of haloperidol according to usual patient care.

In patients treated for more than three days, the dosage will be halved when delirium subsides. When delirium does not reoccur the following day (CAM-ICU remains negative), the dosage will be halved again and then stopped the third day when the patient remains non-delirious. In case delirium occurs again during the reducing phase, the original dose will be restarted.

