### Ethics

The study will be conducted according to the principles of the Declaration of Helsinki (version 2008) and in accordance with the Medical Research Involving Human Subjects Act.

There are indications that early treatment of delirium is more effective than delayed treatment [37], but this needs to be confirmed in other studies. Since it is recognized that the onset of delirium occurs, on average, on day 2 after ICU admission, early preventive treatment is likely to be more effective. In the short-term, low dose haloperidol has no known relevant side effects, therefore randomization and administration of study medication will be started immediately following identification of a high-risk patient. When an informed consent procedure results in a delay of randomization, a deferred consent procedure may be followed. The informed consent procedure will be started as soon as possible, but always within 24 h following ICU admission. If no deferred informed consent can be obtained within 24 h, the patient will be excluded from the study and study drug administration will be stopped.

The medical ethical committee of Arnhem-Nijmegen (CMO) approved this study including this deferred consent procedure (CMO-number 2012/424). This trial is registered on clinicaltrials.gov: NCT01785290.

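### The 24 h side-effect tail overlaps with open-label haloperidol in delirious placebo patients, which dilutes the relative comparison of side effects

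*Protocol article*

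**What the plan says.** Three rules in the protocol article meet here.

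- **Collection window** (Safety monitoring and safety issues): every side effect counts if it arises during "treatment with the study medication until 24 h after stopping the study medication". The same rule covers all arms.
- **End of study drug** (End of study medication): study drug runs to day 28 at the latest and ends earlier at ICU discharge or at delirium. In the case of delirium, "the patient will be treated with open label haloperidol according to the delirium treatment protocol described below". Under Delirium treatment, the general rule is that delirious patients "will be treated with 2 mg haloperidol intravenously three times daily". This equals the dose of intervention group 2. A lower dose is set for named groups, and an increase is allowed for serious agitation or anxiety.
- **Endpoint** (Data collection, Table 2): "Incidence and severity of side effects of prophylactic haloperidol (all patients"). The statistics section gives percentages and a chi-square test for categorical variables, under intention to treat. It states no split at the start of open-label haloperidol and no person-time denominator.

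The article also says that study drug and open-label haloperidol given are recorded, and that QTc time and extrapyramidal signs are checked daily. Non-serious adverse events are collected if the investigator judges them possibly related to study drug. No 24 h limit is stated for serious adverse events, which are the measure for the interim safety looks.

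**The concern.** The endpoint is labelled as side effects of prophylactic haloperidol, but its window includes up to 24 h in which delirious patients in all three arms are on therapeutic haloperidol. In the placebo arm this is the only haloperidol that the trial's rules give, and it falls inside the window. QTc prolongation or extrapyramidal symptoms that it causes can be recorded as placebo events. The overlap may be a sizeable part of a delirious patient's observation, because the Ethics section expects that "the onset of delirium occurs, on average, on day 2 after ICU admission".

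Evaluating side effects is a stated aim and secondary objective 5. The absence of relevant side effects is also part of the argument for adding the higher-dose arm (Background). A placebo rate that contains haloperidol events makes prophylaxis look relatively safer than it is, which is the less cautious direction for a preventive treatment.

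**Working it through.** The plan states no figure for this comparison, so there is none to reproduce. The check is an illustration.

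**Inputs from the article:** delirium risk about 35% (median predicted risk, Background); 75% against 65% delirium in the earlier high-risk study (Background); onset on day 2 on average (Ethics); 24 h tail (Safety monitoring).

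**Assumptions, not in the article:** daily side-effect risk 1% without and 3% with haloperidol; 4 drug days if not delirious; the same delirium rate in both arms; open-label and study haloperidol carry the same daily risk. The second check varies the stay and the rate ratio.

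**1. Proportion with any side effect, 35% delirious.** A delirious patient has 2 drug days plus 1 tail day. A non-delirious patient has 4 + 1 = 5 days.

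As planned:
- Placebo: 0.35 × (1 − 0.99² × 0.97) + 0.65 × (1 − 0.99⁵) = 0.0173 + 0.0319 = 4.9%
- Haloperidol: 0.35 × (1 − 0.97³) + 0.65 × (1 − 0.97⁵) = 0.0306 + 0.0918 = 12.2%
- Ratio 2.5, difference 7.3 points

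Events before the first open-label dose only:
- Placebo: 0.35 × (1 − 0.99²) + 0.65 × (1 − 0.99⁵) = 0.0070 + 0.0319 = 3.9%
- Haloperidol: 0.35 × (1 − 0.97²) + 0.65 × (1 − 0.97⁵) = 0.0207 + 0.0918 = 11.3%
- Ratio 2.9, difference 7.4 points

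Placebo incidence is inflated by about a quarter in relative terms (0.0491 / 0.0388 = 1.26), which is one percentage point. With 75% delirious in both arms, the same formulas give a ratio of 2.05 as planned and 2.93 before open-label.

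**2. Daily rates, over a range.** Let s be the drug days of a non-delirious patient (3, 5 or 8) and p the delirium rate. The open-label share of placebo days is p / [3p + (1 − p)(s + 1)]. A true daily rate ratio R is then observed as R / [1 + share × (R − 1)]. For example, with p = 0.35 and s = 5 the share is 0.35 / 4.95 = 0.071, and R = 3 is seen as 3 / 1.141 = 2.63.

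| Delirium in placebo | Open-label share of placebo days | True 2 seen as | True 3 seen as |
|---|---|---|---|
| 35% | 5–10% | 1.83–1.90 | 2.52–2.72 |
| 75% | 17–23% | 1.62–1.71 | 2.05–2.25 |

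Within a delirious placebo patient, the tail is 1 of about 3 observed days.

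**3. Observation time.** Mean window, haloperidol over placebo, is 1.00 if delirium is equal. It is 1.01–1.04 at 35% against 30% (0.35 × 65/75 = 0.303) and 1.03–1.13 at 75% against 65%. A longer haloperidol window raises raw counts in that arm, against the dilution. For a true rate ratio of 2, the raw count ratio with the tail is 1.85–1.98 (35% against 30%) or 1.68–1.94 (75% against 65%). Without the tail it is 2.04–2.09 or 2.09–2.34. Dropping the tail alone thus leaves a small opposite distortion, which a patient-day denominator removes.

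**The case against.** The strongest reply is that splitting events by treatment phase is analysis-plan content. The analysis plan is not shown, the chi-square sentence is generic, and recorded open-label exposure keeps a split possible if events are dated. This stands in part: nothing rules the split out. But the window and the switch are fixed in the article, and their overlap follows from those rules, not from silence.

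A second reply is that the illustration does not show harm being hidden. This stands. At 715 per arm, the unpooled z is about 5.0 as planned (0.0733 / 0.0147) and 5.3 before open-label (0.0737 / 0.0139). A reader might infer that the window masks harm. The figures support only a diluted ratio with a nearly unchanged absolute difference. They also give every delirious patient the full open-label risk, although some receive a lower dose.

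A third reply is that stopping the count at open-label start censors on delirium, an outcome that treatment may change, and departs from intention to treat. This is weak, because the planned window already ends 24 h after delirium stops study drug. Showing both counts keeps the all-patients comparison.

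The restriction of non-serious events to those possibly related to study drug offers little protection. A blinded investigator does not know whether the stopped drug was haloperidol.

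**Conclusion.** The point holds for the 24 h overlap. Under the article's own rules, events caused by therapeutic haloperidol can count as placebo side effects, and the relative comparison is diluted toward no difference. At the trial's 35% delirium risk the effect is moderate: a risk ratio of about 2.5 in place of 2.9, or a daily rate ratio of 3 seen as 2.52–2.72. It is larger where delirium is more frequent. The sizes rest on assumed daily risks and stays; the direction needs only that haloperidol raises the risk of side effects.

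Two stronger readings are not supported. A reader might infer that observation time differs by arm. One stopping rule applies to all, so times differ only if haloperidol changes delirium, ICU stay or early stopping. If it reduces delirium, the longer haloperidol window acts in the opposite direction. A reader might also infer that the interim safety looks are affected. They use serious adverse events, for which no 24 h limit is stated.

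**What to change.** Leave the 24 h collection and the all-patients incidence as they are. Add to the analysis wording that:

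- the comparison of side effects between prophylaxis and placebo is based on events before the first open-label haloperidol dose;
- events after that dose are tabulated separately by arm;
- events per patient-day at risk are reported by arm, so that any difference in window length is visible.

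No treatment rule changes. Open-label haloperidol is already recorded, and QTc time and extrapyramidal signs are checked daily. The cost is analysis work, provided that events and first open-label doses are dated. The small downside is that some delayed effects of study drug move to the separate table, where they remain visible.

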### Study population

#### **
*Inclusion criteria*
**

All consecutive critically ill patients admitted to the ICU aged ≥18 years at the time of ICU admission and with an expected length of ICU stay of over one day will be included as informed consent is obtained.

Data from patients that are included in the study, but who do not receive any study drug and are discharged from the ICU within 24 h will be discarded from further analysis. Patients who received at least one dose will remain in the study and patients in whom study medication had to be halved or stopped, e.g., because of prolonged QTc time or other side effects, will remain allocated to their study group and analyzed on an intention-to-treat basis.

#### **
*Exclusion criteria*
**

The following will be considered exclusion criteria: no informed consent obtained; history of epilepsy, Parkinson’s disease, hypokinetic rigid syndrome, dementia or alcohol withdrawal syndrome; patients admitted to the ICU for any other neurological disease (including post-cardio-pulmonary resuscitation patients, and patients admitted with coma due to overdose); patients treated with anti-psychotic therapy over the last 30 days prior to ICU admission; prolonged QTc-time (>500 msec) or history of clinically relevant ventricular arrhythmia in last 12 months; pregnancy/breast feeding; documented delirium prior to ICU admission; reasons that impair delirium assessment with the CAM-ICU (serious auditory or visual disorders, unable to understand Dutch or English; severely mentally disabled; serious receptive aphasia); ICU-stay less than one day; moribund and not expected to survive two days; known allergy to haloperidol.

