### Objectives

Definitions of variables in objectives are reported in Table 1.

**Table 1 T1:** Definition of study objectives

**Objective**	**Definition**
*Survival days in 28 days*	Number of days that patients survive in 28 days. All patients will be classified as either ‘alive at study day 28’ or, if dead, ‘dead at study day 28’ on an intention-to-treat basis.
*Delirium diagnosis*	Patients are diagnosed as delirious when they have at least one positive CAM-ICU screening during their complete ICU stay. Patients who were not delirious during their ICU-stay are considered as non-delirious patients.
*Delirium-and-coma-free days in 28 days*	Number of days that the patient is alive and not delirious and not in coma over 28 days starting from the day of inclusion. A delirium-and-coma-free day is defined as a negative CAM-ICU screening with a Richmond Agitation Sedation Score (RASS) greater than (more alert than) -3/-4/-5 during a day. In case a delirious patient is discharged to the ward, a delirium-free day is defined as a delirium observation scale score [30] of less than 3 during a complete day.
*Duration of mechanical ventilation*	Time in days that the patient is on the mechanical ventilator. If the patient is ventilated mechanically several times during one ICU admission, then the ventilator times are added. Both invasive and non-invasive ventilation will be registered. Ventilator-free days (in 28 days) will be calculated.
*Incidence of re-intubation*	Patients who need to be intubated within 28 days from randomization, following a previous extubation, irrespective of the reason for re-intubation, are counted as incident case for re-intubation.
*Incidence of ICU readmission*	Patients who need to be readmitted to the ICU during within 28 days from randomization, irrespective of the reason for readmission, are counted as incident cases for ICU readmission.
*Side effects*	Drowsiness, agitation, QTc-time prolongation (using 12-leads ECG or monitor strip with Bazett’s formula) and development of extra pyramidal symptoms such as tandem gait, dystonia, tremor, myoclonus, tics, rigidity, akathisia [31], determined daily by physical examination by the intensivist.
*Serious adverse event*	Any untoward medical occurrence or effect at any dose that results in one of the following outcomes and is not classified as a clinical outcome of delirium or the underlying disease using the description above:

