	- death that is not related to the underlying disease or sequel of the underlying disease, or death that is considered by the investigator to be related to study drug
	- prolonged inpatient hospitalization or re-hospitalization
	- a life-threatening experience (that is, immediate risk of dying)
	- persistent or significant disability/incapacity
	- congenital anomaly/birth defect
	- considered significant by the investigator for any other reason
*Sudden unexpected serious adverse reactions*	Unexpected adverse reactions are adverse reactions, of which the nature, or severity, is not consistent with the applicable product information. Adverse reactions are all untoward and unintended responses to an investigational product related to any dose administered.

#### **
*Primary objective*
**

To determine the effect of prophylactic haloperidol use on 28-days survival.

#### **
*Secondary objectives*
**

There are seven secondary objectives:

1. To determine the effect of prophylactic haloperidol use on 90-day survival; survival analysis stratifying for delirium incidence will be performed.

2. To determine the effect of prophylactic haloperidol use on the incidence of delirium.

3. To determine the effect of prophylactic haloperidol use on the number of delirium- and coma-free days in a period of 28 days.

4. To determine the effect of prophylactic haloperidol use on delirium related outcomes: time to successful extubation, incidence of re-intubation, incidence of ICU readmission, and incidence of unplanned removal of tubes and catheters.

5. To evaluate the incidence and severity of side effects of haloperidol prophylaxis.

6. To determine the effect of preventive haloperidol use on quality of life 1 and 6 months following ICU admission compared with a baseline measurement at ICU admission using the Short Form-12 (SF-12) questionnaire.

7. *A priori* defined post-hoc analyses:

a. To determine the preventive effectiveness of haloperidol in different patient groups based on the *a priori* risk to develop delirium: patients with a predicted risk up to 50%, 50–70%, 70–90%, above 90% will be evaluated.

a. To determine the preventive effectiveness of haloperidol in different patient groups: medical/surgical/trauma patients, per acute physiology and chronic health evaluation-II (APACHE-II) score (<20, 20–25, >25)

a. Effectiveness of prophylaxis when delirium is diagnosed based on 1, 2, or more days with positive CAM-ICU scoring.

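### The only QTc side effect the article defines is a high-threshold event, although QTc is calculated daily; a numeric between-arm comparison should be named beside it, chiefly because the event can miss small shifts

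*Protocol article*

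**What the plan says.** All references are to the protocol article.

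- **Measurement.** Under Safety monitoring and safety issues, "daily QTc-time is calculated using a 12-lead ECG or a monitor lead ECG".
- **Baseline.** A baseline value has to exist. Study population excludes patients with "prolonged QTc-time (>500 msec) or history of clinically relevant ventricular arrhythmia in last 12 months", and the definition of prolongation refers back to baseline.
- **Definition.** Safety monitoring and safety issues states: "A QTc-time of over 500 msec combined with an increase of over 10% of baseline QTc-time is defined as prolonged QTc-time". The next sentence ties it to treatment: "In case of QTc-time prolongation, the study drug is temporarily stopped until QTc-time is normalized".
- **Use as an outcome.** Table 1 (Objectives) lists among the side effects "QTc-time prolongation (using 12-leads ECG or monitor strip with Bazett’s formula"), without a threshold. Secondary objective 5 is "To evaluate the incidence and severity of side effects of haloperidol prophylaxis", and Table 2 has "Incidence and severity of side effects of prophylactic haloperidol (all patients"). Prolonged QTc is also the first example of a possibly drug-related non-serious adverse event to be collected.
- **Analysis.** Sample size calculation and statistics gives general rules: t-test or Mann-Whitney U for continuous variables, χ² for categorical and binary ones. QTc is not named under either.

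**The concern.** The double threshold suits a decision about one patient. As the only defined measure for comparing arms it uses little of the information collected. A patient who goes from 430 to 495 msec rises by 65/430 = 15% but stays below 500 msec, and so counts the same as a patient with no change. For any baseline above 500/1.1 = 454.5 msec the 10% condition becomes the binding one; at 480 msec the value must pass 528 msec.

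The drug is given preventively to patients without delirium, QTc is singled out for special attention, and the Background expects no relevant side effects at either dose while calling ventricular arrhythmias dose dependent. If the between-arm report rests on the event alone, a non-significant difference could be taken to confirm that expectation while the trial's own daily values would show a modest shift.

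**Working it through.** **The plan's own figure.** There is none for QTc. The only power calculation is for survival, and it supplies the group size used here. It reproduces: with medians 18 and 0.85 × 18 = 15.3 days, 90 days of accrual and 28 of follow-up, the event probabilities are 0.905 and 0.932, and n = (1.96 + 0.84)² × (1/0.905 + 1/0.932) / (ln 0.85)² ≈ 647 per group (unrounded inputs).

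**Inputs.**
- From the article: 647 per group, two-sided 0.05, baseline at most 500 msec, event = above 500 msec and above 1.1 × baseline.
- Assumed, because the article gives no QTc distribution: baseline normal with mean 430 or 445 and SD 30 msec; change normal with SD 25, 35 or 45 msec; the same shift in every treated patient; 1, 3 or 5 readings per patient. With several readings, half the change variance is between patients, and any qualifying reading makes the patient an event.

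**Formulas.**
- Event: power = Φ(|p1 − p0| / √[(p0(1 − p0) + p1(1 − p1))/647] − 1.96), with p0 and p1 from simulation.
- Numeric: power = Φ(d / (s√(2/647)) − 1.96), with √(2/647) = 0.0556. Here s is the SD of a patient's mean change: the SD of change for one reading, and SD × √(0.5 + 0.5/k) for k readings.

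**Two worked cases.**

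1. One reading, baseline 430, SD of change 25, shift 5 msec.
   - Event: p0 = 0.99%, p1 = 1.57%; 0.0058/0.00625 = 0.93; Φ(−1.03) = 15%.
   - Numeric: 5/(25 × 0.0556) = 3.60; Φ(1.64) = 95%.
2. Five readings, baseline 445, SD of change 25, the setting kindest to the event.
   - Shift 5 msec: p0 = 5.50%, p1 = 8.16%; power about 47%. Numeric, with s = 25 × √0.6 = 19.4: above 99%.
   - Shift 10 msec: p1 = 11.67%; event power about 98%, numeric 100%.

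**Full range over the assumed means and SDs.**

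| Shift | Readings | Event | Numeric change | Gap in points |
|---|---|---|---|---|
| 5 msec | 1 | 15–22% | 51–95% | 32–80 |
| 5 msec | 3–5 | 27–48% | 69–100% | 37–72 |
| 10 msec | 1 | 50–69% | 98–100% | 31–50 |
| 10 msec | 3–5 | 77–98% | about 100% | 2–23 |

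Placebo event rates in these settings run from about 1% (one reading) to 27% (five readings, SD of change 45), so the assumptions do not uniformly make the event rare. Stated as rates, 647 per group gives 32% power for 1% against 2%, 56% for 2% against 4%, and 93% for 5% against 10%.

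**The case against.** The strongest reply has four parts.

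1. *The threshold sentence defines a stopping trigger, and nothing limits the comparison to it.* A reader might infer that the plan commits QTc to a χ² test of this event and nothing else. The documents do not support that. Table 1 carries no threshold, objective 5 and Table 2 speak of severity as well as incidence, and the rule for continuous variables could be applied to QTc. This stands, and the point is limited accordingly. What remains is that prolonged QTc is also used as a side-effect outcome, that its only definition is the double threshold, and that neither severity nor any summary of the daily values is expressed in msec.

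2. *How to summarise daily ECG values is ordinary SAP detail.* Partly right: the full protocol and SAP are not shown and may already contain a numeric analysis. But the article itself sets the scale of the one QTc outcome it defines, so it is fair to ask for the companion analysis if it is not there already.

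3. *A single-reading calculation understates the event.* This stands. Because any daily reading can qualify, event power rises with more readings, and at 10 msec the gap can fall to about 2 points.

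4. *The event answers a legitimate question, and on-drug readings are selective.* Both stand. The incidence of values above 500 msec is of interest in its own right, and no passage says that a 5 msec mean shift matters clinically. Readings on study drug end at delirium or ICU discharge, and dosing is interrupted by QTc itself. The numeric comparison should therefore be added and not substituted, and its limits stated.

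**Conclusion.** The point holds as a modest, low-cost improvement. The article has daily and baseline QTc available, defines only a high-threshold event as the QTc side effect, and names no numeric comparison. In every setting computed, the numeric change has more power for the same shift. The gain is about 32–80 points at 5 msec. At 10 msec it is anywhere from about 2 to 50 points, depending mainly on how many readings each patient contributes.

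A reader might go further and conclude that the trial has little power to show QTc prolongation. That does not follow. No QTc rate or SD is given, and for a 10 msec shift the event itself reaches 77–98% power with 3 to 5 readings.

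The figures assume normal values, one common shift and complete readings. They ignore drug interruptions and the loss of readings at delirium or discharge. They show the direction and rough size of the loss and do not predict this trial's power.

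**What to change.** Leave the threshold event, its reported incidence and the stopping rule unchanged. If the SAP does not already do so, add to secondary objective 5 and to the statistics section a between-arm comparison of numeric QTc, each dose against placebo, adjusted for baseline QTc. One suitable form is a repeated-measures model over the first treatment days, using readings before any open-label haloperidol, reported as a mean difference in msec with a 95% CI.

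Two conditions should be written down. Readings taken while study drug is interrupted for QTc stay in the analysis, because dropping them would select on the outcome. The report should also note that readings cut off by delirium or ICU discharge limit interpretation.

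The cost is one or two sentences and one more safety analysis. No extra ECGs are needed, but baseline and daily QTc must be entered in the E-CRF as numbers and not only as prolonged yes/no; the article does not say which is planned.
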